## Abstract

**Background:**

There are often disparities between current evidence and current practice. Decreasing the gap between desired practice outcomes and observed practice outcomes in the healthcare system is not always easy. Stopping previously recommended or variably recommended interventions may be even harder to achieve than increasing the use of a desired but under-performed activity. For over a decade, aspirin has been prescribed for primary prevention of cardiovascular disease and for patients with the coronary artery disease risk equivalents; yet, there is no substantial evidence of an appropriate risk-benefit ratio to support this practice. This paper describes the protocol of a randomized trial being conducted in six primary care practices in the Denver metropolitan area to examine the effectiveness of three interventional strategies to change physician behavior regarding prescription of low-dose aspirin.

**Methods:**

All practices received academic detailing, one arm received clinician reminders to reconsider aspirin, a second arm received both clinician and patient messages to reconsider aspirin. The intervention will run for 15 to 18 months. Data collected at baseline and for outcomes from an electronic health record will be used to assess pre- and post-interventional prescribing, as well as to explore any inappropriate decrease in aspirin use by patients with known cardiovascular disease.

**Discussion:**

This study was designed to investigate effective methods of changing physician behavior to decrease the use of aspirin for primary cardiovascular disease prevention. The results of this study will contribute to the small pool of knowledge currently available on the topic of ceasing previously supported practices.

**Trial Registration:**

ClinicalTrials.gov: NCT01247454

## Background

Cardiovascular disease is the leading cause of death for men and women in the United States. In 2002, the United States Preventive Services Task Force (USPSTF) began recommending low-dose aspirin as a primary prevention measure in patients at high risk of developing coronary artery disease [1]. However, there are many well-designed studies that do not support the use of aspirin for primary prevention of cardiovascular events in patients with no known coronary artery disease [2-6], including patients with conditions considered to confer a risk equivalent to coronary artery disease, such as diabetes [7-9], peripheral artery disease [7], and chronic kidney disease [10]. Meta-analyses of many studies have also shown inconsistent results [11-13]. In addition to the uncertainty of efficacy, research has shown that the benefits of low-dose aspirin for primary prevention may not appropriately outweigh the harms [14]. The Food and Drug Administration (FDA) has denied requests to approve aspirin for the primary prevention of cardiovascular events twice, once in 1998 and again in 2003, due to lack of evidence supporting its efficacy [15,16]. Since 2003, no new large studies that support the use of low-dose aspirin therapy have been published, though several that do not demonstrate a protective effect of low-dose aspirin have been completed [4,7,8,10]. However, aspirin has continued to be recommended for this use by the American Heart Association [17], the USPSTF [18], the American Stroke Association [17], and the American Diabetes Association [19], and is prescribed for primary prevention by physicians worldwide.

There is often a disparity between current evidence and current practice, but making changes to the system can prove difficult. Research has revealed that physicians' behavior is relatively resistant to change due to a variety of internal and external factors [20-24]. However, some interventional methods have been more efficacious than others. Mere passive dissemination of information is typically ineffective, whereas active interventions have been shown to be more successful [25-27]. While many physicians believe that clinical guidelines are beneficial to their practice and patient outcomes [28,29], clinical guidelines alone do not seem to impact physician behavior [30]. Furthermore, guidelines that recommend the elimination of old behavior may be more difficult to implement than guidelines that recommend the addition of a new behavior [21].

Sittig, *et al. *conducted a study to test clinical decision support systems on reducing the use of inappropriate medications in various groups of patients [24]. The study added to the evidence that clinical decision support systems are effective [25,31,32]. Reminders that utilize similar electronic systems [27,30,31,33-35] and educational outreach (*i.e.*, academic detailing) [25-27,30,34,36] have produced significant results. Interventions that are patient mediated have been successful as well [25]. Multi-faceted techniques involving two or more interventions have also proven more effective than single interventions [25-27,30,34,36].

Until recently, all primary care physicians within the University of Colorado Hospital ambulatory system received reminders through a clinical decision support system to consider aspirin therapy for all patients with diabetes mellitus, peripheral artery disease, chronic kidney disease, or a calculated Framingham Risk Score >20%. Based on the lack of evidence supporting this practice, the group of Family Medicine and General Internal Medicine physicians overseeing this system decided to remove the reminder message from the electronic medical record. No active, systematic approach to stop this previously recommended behavior has been undertaken. Members of the Clinical Decision Support group indicated that they believe simply discontinuing the recommendation would have no impact on clinical care, and that the use of low-dose aspirin for primary prevention would otherwise continue. Therefore, this study was designed to actively disseminate to clinicians the new University of Colorado Hospital primary care recommendations regarding the use of aspirin for primary prevention.

The aims of this project are:

1. Assess the current use of aspirin therapy for primary and secondary cardiovascular disease prevention in six General Internal Medicine and Family Medicine clinics within the University of Colorado Hospital system using electronic health record data;

2. Develop messages concerning the appropriate use of aspirin for cardiovascular disease prevention for academic detailing to clinicians, a point-of-care decision support aid for clinicians, and a patient activation form; and

3. Test the effectiveness of these interventions to improve the evidence based use of aspirin for primary and secondary prevention of cardiovascular disease using a three arm randomized trial.

The three intervention arms will be as follows:

1. Academic detailing only;

2. Academic detailing plus a message to the physician in the clinical decision support system asking the clinician to reconsider the aspirin therapy; and

3. Academic detailing, plus the physician message, plus a patient activation form that includes a message to the patient to ask his or her physician about use of aspirin for primary prevention.

The academic detailing presentation (http://www.dartnet.info/media/LowDoseASAandCVDpreventionSlides.pdf) and one page information sheet (http://www.dartnet.info/media/LowDoseASAEvidenceSummaryforClinicians.pdf) are available online.

The null hypotheses for the project, stated as null hypotheses are:

1. There will be no significantly different decrease in the use of low-dose aspirin therapy for primary prevention across the three intervention arms from baseline to completion of the project;

2. There will be no significant differences in the percentage of patients with diabetes mellitus over age 44 years on low-dose aspirin therapy for primary prevention across the three arms of the study, as shown by repeated measures from baseline to completion of the project; and

3. There will be no significant difference in the percentage of patients with known ischemic heart disease treated with low-dose aspirin between the three arms of the study at baseline and at the end of the study (*i.e.*, there will be no erosion in the appropriate use of aspirin due to the intervention to decrease aspirin use for primary prevention).

## Design and methods

### Design

This project is primarily designed as comparative effectiveness trial with all intervention sites receiving education concerning a system wide decision to stop recommending aspirin for primary prevention of cardiovascular disease. Six University of Colorado primary care practices in the Denver metro area were block randomized by baseline number of patients on aspirin for primary prevention into one of three intervention arms:

1. Academic detailing and cessation of the primary prevention reminder within the point-of-care clinical decision support system only;

2. Academic detailing with a message asking clinicians to consider stopping aspirin therapy for primary prevention embedded in the point-of-care clinical decision support system; or

3. Academic detailing with the point-of-care message for clinicians as described in arm two above, and a short patient activation form to be given to patients prior to a visit, which asks them to check with their provider concerning their use of aspirin for primary prevention.

The academic detailing consisted of a presentation to the clinicians and staff of each office by the study principal investigator and co-investigator (for larger practices more than one presentation was made), as well as the development and distribution to all primary care clinicians of a one-page information sheet concerning the lack of evidence for low-dose aspirin for primary prevention of cardiovascular disease (CVD). The patient activation form, shown in Additional File 1, was requested by one of the primary care practices prior to this study. All messages on the form, including the aspirin message, were reviewed by clinicians from all primary care practices. Practices were free to request that the forms be turned off at any time during the study, but none did so.

One primary care practice in the system elected to not receive the academic detailing or to participate in the project. This practice will be utilized as a non-randomized temporal control for the intervention practices. An interim analysis will be conducted at six months and the final analysis will be conducted at 15 to 18 months.

All practices involved in the study were divided into three groups to match the number of patients at baseline on aspirin for primary prevention as closely as possible. After the academic detailing was completed at all sites, practice names were placed on identical cards and blindly drawn from a box by a study team member to allocate them to the patient activation, clinician-only reminder, and academic detailing alone groups. The consort diagram of number of patients randomized to each intervention is shown in Figure 1.

**Figure 1 F1:**
[figure not shown]
**CONSORT diagram of the study**.

### Participants

Pre-intervention data were collected through the electronic medical record system (N = 6,827). Patients were separated into categories based on two criteria as listed in their charts: a once daily dosing of low-dose aspirin and a diagnosis of CVD based on appropriate International Classification of Disease, Ninth Revision (ICD-9) codes (both coronary artery disease and thrombotic cerebrovascular disease). Persons who met both criteria were classified as 'CVD and on aspirin' (N = 1,763). Persons who met the criteria of low-dose aspirin but had no associated cardiovascular diagnosis were classified as 'No CVD but on aspirin' (N = 4,400). Those who had no documentation of aspirin or other anti-platelet therapy, but who carried a cardiovascular diagnosis were classified as 'CVD but not on aspirin' (N = 664). The study is targeted to change care in the 'No CVD but on aspirin' group specifically, but will observe the 'CVD and on aspirin' and 'CVD but not on aspirin' groups to monitor for any change, particularly an unwanted drop in use of anti-platelet aspirin therapy in patients with known CVD.

For the outcome variable of change to recommended aspirin therapy, a sample size of 800 per arm provides 80% power to detect a 7% difference between any two groups. We believe that any change under 10% is not clinically significant; therefore, the ability to show an even smaller statistically significant change indicates that this study has enough power to detect meaningful change in aspirin therapy.

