## Discussion

One of the six practices withdrew from the study prior to the randomization and implementation of the interventions, reducing the patient size (N = 6,016). For this practice, the primary prevention reminder was stopped within the point-of-care clinical decision support system. This practice was treated as a non-randomized temporal control for the intervention practices. Even without randomizing this practice, the power of the study will remain sufficient.

Much research has been done regarding physician behavior change and implementation of new techniques, treatment, and therapies. However, there is not a great deal of literature surrounding effective methods for discontinuation of current practices. Effecting a change in aspirin usage in one or more groups will result in a better understanding of the approaches and efforts needed to stop the use of a previously recommended therapy. If a change in aspirin usage is not detected, a follow-up qualitative analysis at the provider level may provide a better understanding of why providers and patients were unwilling to stop a potentially harmful treatment.

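### The 80% power for a 7-point difference matches a calculation for independent patients and is unsupported for about five allocated practices, so the claim that power remains sufficient is also unsupported

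*Protocol article*

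**What the plan says.** The Participants section states that "a sample size of 800 per arm provides 80% power to detect a 7% difference between any two groups". It adds "We believe that any change under 10% is not clinically significant" and reasons that "the ability to show an even smaller statistically significant change indicates that this study has enough power". It gives no base cessation rate, significance level, ICC, design effect or number of practices for this calculation.

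The Design section describes allocation by practice: "practice names were placed on identical cards and blindly drawn from a box by a study team member". It also says that "Six University of Colorado primary care practices in the Denver metro area were block randomized by baseline number of patients on aspirin" for primary prevention. The Discussion says that "One of the six practices withdrew from the study prior to the randomization and implementation of the interventions", reports the loss as a fall in patients to N = 6,016, and concludes: "Even without randomizing this practice, the power of the study will remain sufficient".

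The Data analysis approach section puts the analysis at the patient level with clinic as a fixed effect. It notes that the clinics are too few for stable variance components, and plans a further model with physician as a random effect.

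**The concern.** The unit of allocation is the practice, and the interventions act through clinicians and clinic systems. Patients in the same practice can therefore be expected to have correlated outcomes. Power then depends mainly on the number of practices and on how much they vary, and much less on the number of patients. The power statement mentions neither.

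The Discussion treats the withdrawal as a loss of patients only, when it also removes one of six units of allocation. Five practices in three arms split 2-2-1 or 3-1-1, so at least one arm would be a single practice. That arm's effect could not be separated from the practice itself.

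What is at stake is how the result is read. The article uses the figure to vouch for detecting changes smaller than its own 10% threshold. A null comparison could then be taken as evidence that the three strategies perform alike, when the design may have had little chance of telling them apart.

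**Working it through.** **1. Reproducing the stated figure.** The stated inputs are 800 per arm, 80% power and 7 points. Assumed inputs are a two-sided 5% level and rates of 46.5% v 53.5% (maximum variance).

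n = [1.96·√(2·p̄(1−p̄)) + 0.842·√(p1(1−p1) + p2(1−p2))]² / (p1−p2)² = 799.7, so 800 per arm.

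No design effect is needed to reach 800. The same formula gives 575 per arm at 20% v 27%, 373 at 10% v 17% and 248 at 5% v 12%.

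**2. Practice size (assumed).** The primary cohort before withdrawal is 4,400 of 6,827 (Participants), and 6,016 remain (Discussion). Pro rata, 4,400 × 6,016 / 6,827 = 3,877. Over five practices this is about m = 775 each, assuming equal sizes and that the withdrawn practice had a proportional share of the cohort.

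**3. Power with allocation by practice.** With k1 and k2 practices in the two arms compared, and p̄ the mean of the two rates:

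SE = √{ p̄(1−p̄) · [ICC + (1−ICC)/m] · (1/k1 + 1/k2) }

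Power comes from δ = difference/SE, by the normal distribution and by a noncentral t with 5 − 3 = 2 df (critical value 4.30).

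Example: 7 points, p̄ = 0.5, m = 775, ICC 0.01, two v two. The bracket is 0.01 + 0.99/775 = 0.01128; SE = √(0.25 × 0.01128 × 1) = 0.0531; δ = 0.07/0.0531 = 1.32. Power is 26% by normal theory and 13% on 2 df.

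| Difference, mean rate | Practices | ICC | Normal | 2 df |
|---|---|---|---|---|
| 7 points, 50% | 2 v 2 | 0.001 | 83% | 37% |
| 7 points, 50% | 2 v 1 | 0.001 | 67% | 28% |
| 7 points, 50% | 2 v 2 | 0.01 | 26% | 13% |
| 7 points, 50% | 2 v 1 | 0.01 | 19% | 10% |
| 10 points, 50% | 2 v 2 | 0.001 | 99% | 60% |
| 10 points, 50% | 2 v 2 | 0.003 | 86% | 40% |
| 10 points, 50% | 2 v 2 | 0.01 | 47% | 20% |
| 7 points, 10% v 17% | 2 v 2 | 0.001 | 99% | 61% |
| 7 points, 10% v 17% | 2 v 2 | 0.01 | 49% | 21% |

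**4. What the ICC means here.** At a mean rate of 50%, the between-practice standard deviation is √(0.25 × ICC): 1.6 points at ICC 0.001 and 5 points at 0.01.

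**5. How small the ICC must be.** For two v two, 775 each and normal theory, 80% power for 7 points near 50% needs a design effect of at most 1,550/800 = 1.94. Since the design effect is 1 + 774·ICC, the ICC must be at most 0.94/774, about 0.0012. For 10 points (392 per arm unclustered) the limit is (1,550/392 − 1)/774, about 0.004. At 10% v 17% it is (1,550/373 − 1)/774, also about 0.004.

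**6. If six practices were randomised.** Taking the article's 800 per arm as two practices of 400 with 3 df, power for 7 points near 50% is 48% at ICC 0 and 15% at ICC 0.01 (80% and 24% by normal theory). The conclusion does not turn on five v six.

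**The case against.** **The unclustered basis is inferred.** A reader might take it as proved that the authors ignored clustering. The documents do not show that. At 20% v 27% the unclustered size is 575, so 800 would also fit a design effect of 1.4; at 10% v 17% it would fit 2.1. The unclustered reading is the simplest, because it lands on 800 with no further adjustment, but it is not stated. This stands, and it is why the claim is called unsupported and not simply wrong.

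**Rates near 50% are the worst case, and the cohort exceeds 800 per arm.** Both are true. A reader might infer that the trial lacks power even for the 10-point change. The table does not support that flatly: by normal theory, two v two, power for 10 points is 86% or more up to ICC 0.003. It falls below 80% at larger ICCs, and at these rates on 2 df throughout.

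**Three pairwise comparisons.** Bonferroni alone would cut 80% to 66%, and it is tempting to add this loss. The first null hypothesis is a single comparison across three arms, and with three groups unadjusted pairwise tests after a significant overall test control the familywise error. No multiplicity loss is counted here.

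**The analysis section recognises clinics.** It does, but that does not rescue the power figure. Clinic is nested in arm: with five clinics, an intercept, two arm terms and four clinic terms make seven columns of rank five, so arm effects cannot be estimated alongside full clinic effects. The planned random effect is for physician, not practice.

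**Conclusion.** The concern holds in a limited form. The 80% figure and the statement that power stays sufficient have no stated support for a design that allocates about five practices to three arms. By normal theory they fail unless the ICC is around 0.001 at rates near 50%, or a few thousandths at lower cessation rates. With 2 practice-level degrees of freedom and rates near 50%, power for 7 points is only 55% (two v two) or 42% (two v one) even at ICC 0. Nothing in the article shows that between-practice variation is that small.

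The size of the shortfall rests on assumptions that the article does not settle: the ICC, the base rate, equal practices of about 775, and the split by arm (the participant-flow figure is not available). The direction does not: at any fixed base rate and number of patients, positive between-practice variation lowers power, and few practices lower it further.

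**What to change.** - Replace the 80%/7-point statement and the sentence that power remains sufficient with clustering-adjusted power or detectable differences for the practices actually randomised. Show them over stated ranges of ICC (for example 0.001 to 0.05) and base cessation rate, with practice-level degrees of freedom.
- Reconcile the Design section's six randomised practices with the withdrawal described in the Discussion, and state how many practices are in each arm.
- State that a null between-arm result cannot be read as equivalence of the strategies.
- Report arm contrasts with intervals that reflect allocation by practice, and say so where an arm is a single practice.

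The cost is text only: no added patients or sites. The downside is a less favourable stated figure.

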### Data collection

Our pre-intervention data were collected using the University of Colorado Hospital's Allscripts database and the QED Clinical, Inc. (DBA-CINA) Clinical Data Repository maintained by the Department of Family Medicine. Our post-intervention data will be collected using the same system. The intervention will run for 15 to 18 months.

The primary analysis will include only patients identified as being on aspirin prior to 1 April 2009, when the decision support aspirin message was changed. Aspirin therapy status will be evaluated at six and twelve months after the intervention is initiated at each site. The outcome variable for the analysis will be presence/absence of aspirin therapy at final observation time. We will use a logistic regression approach to determine whether likelihood of aspirin cessation differs among treatment groups, adjusting for clinic (fixed effect), and patient clinical and sociodemographic covariates (age, gender). Time from baseline to last observation will be included as a covariate in the primary analysis. Patients who do not have a follow-up visit during this period will initially be excluded from the analysis, but a sensitivity analysis will be performed, assuming patients with no follow-up visit are still on aspirin therapy. Clinic will initially be included as a fixed effect in analyses because the total number of clinics is too few to achieve stable estimates of covariance components for multilevel modeling. However, additional analyses will be carried out using multilevel modeling with patients nested within physicians because there are an adequate number to include physician as a random effect. Additionally, we will explore using a Cox proportional hazards model with time to cessation as the outcome.

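### The primary model puts arm beside clinic fixed effects although clinic is nested in arm, so the arm effect is not estimable; without the clinic term, practice differences in stopping enter the arm contrast and the patient-level standard error omits them

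*Protocol article*

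**What the plan says.** All places are in the Protocol article.

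- **Allocation (Design).** The practices were "divided into three groups to match the number of patients at baseline on aspirin for primary prevention as closely as possible", and then "practice names were placed on identical cards and blindly drawn from a box by a study team member". The practice is the unit of allocation. The balancing factor is the count of aspirin users, not the rate at which practices stop aspirin. The draw followed completion of the detailing at every site.
- **Number of practices.** Design says six were randomized. The Discussion says one of the six withdrew before randomization and became a non-randomized temporal control, which leaves five.
- **Cohort (Data analysis approach).** "The primary analysis will include only patients identified as being on aspirin prior to 1 April 2009, when the decision support aspirin message was changed".
- **Outcome and model (same section).** "The outcome variable for the analysis will be presence/absence of aspirin therapy at final observation time". It is analysed at patient level by logistic regression on treatment group, adjusting for clinic, age and gender. "Time from baseline to last observation will be included as a covariate in the primary analysis". On the clinic term: "Clinic will initially be included as a fixed effect in analyses because the total number of clinics is too few" for stable multilevel variance estimates.
- **Other analyses.** A model with physician as a random effect is additional, a Cox model is exploratory, and the comparison with the control practice is secondary.
- **Abstract, Methods.** "Data collected at baseline and for outcomes from an electronic health record will be used to assess pre- and post-interventional prescribing".

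**The concern.** With whole practices allocated and at least one arm made up of a single practice, differences between practices are likely to be the main source of error. How often a practice takes aspirin off its medication lists depends on reconciliation habits, staffing and case mix, and part of that is likely to persist over time. Matching on patient counts does not address it, and neither do age, gender or follow-up time.

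The clinic fixed effect looks like the safeguard, but every clinic belongs to exactly one arm. Once each clinic has its own intercept, no information is left about arm. Software will either fail or silently drop terms. If it drops clinic terms, the arm coefficient becomes a contrast between reference clinics. If the team drops clinic altogether, the coefficient is the arm effect plus whatever separates the practices, with a standard error that counts patients only. At stake is whether a reported difference between detailing, clinician prompts and patient activation can be told apart from a difference between practices.

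**Working it through.** **1. The plan's own figure.** Participants states 800 per arm for 80% power to detect a 7-point difference. The base rate, alpha and sidedness are not given; I assume a rate near 50% and two-sided 5%.

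n = [1.96·√(2·p̄·q̄) + 0.8416·√(p1q1 + p2q2)]² / d²

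For 46.5% v 53.5%: (1.3859 + 0.5937)² / 0.0049 = 800. For 50% v 57% it is 796. The figure therefore reproduces as an individually randomized comparison with no practice variance.

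**2. Can the stated model estimate arm?** Columns: intercept, two arm terms, and one fewer clinic term than there are clinics.

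| Practices per arm | Columns | Rank | Arm contrast estimable |
|---|---|---|---|
| 2/2/1 | 7 | 5 | no |
| 3/1/1 | 7 | 5 | no |
| 2/2/2 (six, as in Design) | 8 | 6 | no |

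With a historical period added, the columns for five practices are intercept, four clinics, period and two arm-by-period terms. That is 8 columns and rank 8, in both 2/2/1 and 3/1/1. Five practice-level changes less three arm means leave 2 residual degrees of freedom.

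**3. Clinic dropped, patient-level standard error kept.** The documents give no practice-level stopping rates, so the practice SD and the base rate are assumptions. For two practices v one at 800 per arm, in squared percentage points:

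- patient variance s² = p(100 − p)·(2/800)
- true variance v = s² + SD²·(1/2 + 1)
- false-positive rate = 2·[1 − Φ(1.96·√(s²/v))]

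| Base rate | SD | s² | v | False-positive rate |
|---|---|---|---|---|
| 10% | 2 | 2.25 | 8.25 | 31% |
| 10% | 3 | 2.25 | 15.75 | 46% |
| 20% | 2 | 4.00 | 10.00 | 22% |
| 20% | 3 | 4.00 | 17.50 | 35% |

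**4. What a historical period buys.** Assume about 775 patients per practice (4,400 × 6,016/6,827 = 3,877; divided by 5 = 775, taking the withdrawn practice to have had the average mix) and 20% stopping. Sampling variance per practice is e = 20·80/775 = 2.06. For two practices v one, with r the correlation of a practice's rate between periods:

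- SE(level) = √[1.5·(SD² + e)]
- SE(change) = √{1.5·[2(1 − r)·SD² + 2e]}

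| SD | SE(level) | SE(change), r = 0.8 | Difference | SE(change), r = 0.5 | Difference |
|---|---|---|---|---|---|
| 6 | 7.56 | 5.27 | −30% | 7.76 | +3% |
| 4 | 5.21 | 3.97 | −24% | 5.49 | +6% |
| 2 | 3.02 | 2.93 | −3% | 3.49 | +16% |

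**5. What remains.** With 2 degrees of freedom the 95% multiplier is 4.30. At SD 6 and r = 0.8, practice variation alone gives SE = 6·√0.4·√1.5 = 4.65, so ±20 points. With sampling error, 4.30 × 5.27 = ±22.7 points. On levels it is 4.30 × 7.56 = ±32.5 points.

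**6. Is a practice-level standard error still needed?** Yes. In a simulation of the three-arm test (2/2/1, about 1,292 patients per arm, 10% or 20% base rate), a patient-level test of change with 80% of practice variance persistent still rejected falsely 12% to 18% of the time at SD 2 and 23% to 34% at SD 3. Only full persistence brought it to about 5%.

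**The case against.** The strongest reply is that comparing final status between randomized groups is a legitimate estimand. The draw was random, so practice differences are chance error that belongs in the standard error, and a change analysis is a design preference. As far as the estimand goes, this stands: a level comparison with practice-level standard errors would be valid. But the plan specifies neither that standard error nor a model in which arm can be estimated. The physician random effect and the Cox model do not separate practice from arm either.

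Several stronger readings are tempting and are not supported:

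- **That the outcome contradicts the Abstract's pre/post statement or the first null hypothesis.** It does not. Everyone in the cohort is on aspirin at baseline, so the final stopping proportion is the decrease from baseline.
- **That the model as written passes practice differences directly into the arm effect.** As written it yields no arm effect. The contamination arises once clinic terms are dropped, by software or by choice.
- **That the twelve months before the draw would serve as the pre-period.** Detailing was complete before the draw and is part of every arm, and the window might also straddle the 1 April 2009 message change. Such a window is not pre-intervention.
- **That the control-practice comparison gains automatically.** That practice declined detailing. A pre-window containing detailing would subtract part of its effect from the intervention practices only.
- **That a historical period rescues the trial.** It removes only the persistent part of practice differences. Persistence is itself uncertain, because the earlier period ran under a reminder to consider aspirin.

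**Conclusion.** The point holds as a fault in the stated primary model. Arm and clinic fixed effects cannot both be estimated with five practices, or six, each in one arm, and this needs no assumption. If the clinic term is removed and nothing else changes, the arm contrast carries practice differences that the patient-level standard error leaves out. The direction of that error is certain. Its size (22% to 46% false positives at nominal 5%) depends on the assumed practice SDs of 2 to 3 points and base rates of 10% or 20%.

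Historical data make arm-by-period estimable beside clinic. The precision gain is conditional: useful at SD 4 to 6 with correlation 0.8, negligible at SD 2, and slightly negative at correlation 0.5 or below. On any of these assumptions the intervals remain wide against the 7-point target and the 10-point threshold for clinical significance in Participants. The 2/2/1 layout is inferred, since the CONSORT figure is not shown; 3/1/1 would leave two single-practice arms.

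**What to change.** 1. **Historical cohort.** From the same electronic record and repository, build for every practice, including the control, a cohort without CVD and on aspirin at the window start, with status read at the window end. Use the same window length in all practices, ending before both the detailing and 1 April 2009.
2. **Model.** Make the primary arm effect the arm-by-period term in a logistic model with clinic fixed effects and period. Take its standard error from the five practice-level changes, with 2 degrees of freedom.
3. **Fallback.** If the repository does not reach back far enough, drop the clinic term and compare arms on practice-level stopping rates with practice-level standard errors.
4. **Stated limits.** Say that only persistent practice differences are removed, that the gain depends on year-to-year correlation, and that the control comparison benefits only if the pre-window excludes detailing.
5. **Number of practices.** Reconcile Design (six randomized) with the Discussion (five), and give the number per arm.

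The cost is one retrospective data pull and a revised model statement. How far back the repository reaches is not stated. The main downside is a small loss of precision if practice rates correlate weakly over time.
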